### Implementation, service utilisation and costs

#### Economic Evaluation

Murphy et al., strongly recommend that cost-effectiveness is considered as an outcome as none of the studies in their review of psycho-educational interventions with adolescents addressed it [39]. We will therefore weigh up the diabetes related costs and consequences of the different interventions (that involve resource use) from an NHS perspective. Contacts with NHS services and resource use will be collected via questionnaire. Costs will be obtained from national sources. Activity will be collected for 6 months.

#### Process evaluation

Following the intervention, sixty children/young people and parents (as appropriate) will be interviewed by telephone or in person (40 from the intervention group and 20 from the control group) in order to gain further understanding about implementation issues, and user experiences of the intervention diabetes diaries and information packs or resources used in existing routine practice.

Healthcare professionals associated with the care of children/young people recruited to the trial will also be invited to complete a semi-structured questionnaire to determine acceptability and impact of the new diabetes diaries and information pack in practice.

#### Data handling

SPSS^® ^and Atlas Ti^® ^will be used for statistical, qualitative and healthcare professional questionnaire data handling [40,41]. NWORTH will support data management and processing. Where appropriate, we plan to use an electronic data collection system (TrialSys^® ^) in each centre with an alternative paper-based system [42]. Data will be transmitted securely electronically to the clinical trials unit NWORTH [43].

#### Data analysis

##### Statistical analysis

Initial descriptive statistics will describe characteristics and demographics of the sample at baseline. We shall compare outcomes between the two groups by analysis of covariance to adjust for possible differences in baseline measurements. This will be repeated at 3 and 6 months comparing intervention and control groups. In addition, longitudinal analysis will consider any changes over time. These analyses will examine changes in the quality of life measures (paediatric EQ-5D, PedsQL generic and diabetes-specific health measures) over baseline, both using a pairwise comparison, studying change on individuals, and a cohort analysis comparing overall change in group means.

Multiple regression analyses will be performed to identify factors which predict good outcomes within and between groups.

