#### Sample size calculation and effect size

A systematic review provides sample size calculations for studies of educational interventions targeting psychological effects and glycaemic control (HbA1c) for children with diabetes [39]. They calculated a total of 130 randomized subjects in order to detect a 0.5 (medium) psychological effect size, with a power of 80% at the 0.05 significance level (assuming equal assignment in the two arms). They report that the effect size for psychological outcomes is more predictable with a median and mean of 0.38 and 0.35 respectively, therefore we will aim to detect an effect size of 0.4.

The sample size is 252 children/young people with type 1 diabetes (this is allowing for a 10% drop out rate, and adjusting for a 2:1 randomisation strategy). In order to gain more experience of the new intervention in routine practice, we will employ a 2:1 randomization strategy and randomise 168 children/young people into the intervention arm and 84 children/young people into the non intervention arm, stratified by age, gender and length of time since diagnosis (< 2 years and > 2years). Figure 1 shows the flow of patients through the trial.

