##### Randomisation

A web-based, password protected, secure adaptive randomisation with a telephone backup has been developed.

168 children/young people will be randomized into the intervention arm and 84 children/young people into the no intervention arm, stratified by gender, length of time since diagnosis (< 2 years and > 2 years) and age (stratification by age will be into the following age categories: 6-10 years; 11-15 years; and 16-18 years).

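### The stated ANCOVA adjusts for baseline measurements but does not name the three factors on which randomisation is balanced; if those factors are prognostic, the reported standard error is modestly too large and the test conservative

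*Protocol article*

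**What the plan says.** Protocol article, Randomisation: allocation is "stratified by gender, length of time since diagnosis (< 2 years and > 2 years) and age", with three age bands (6-10, 11-15 and 16-18 years). The method is described thus: "A web-based, password protected, secure adaptive randomisation with a telephone backup has been developed". Sample size calculation and effect size lists the same three factors.

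Protocol article, Statistical analysis, gives the between-group model and its adjustment: "We shall compare outcomes between the two groups by analysis of covariance to adjust for possible differences in baseline measurements". The comparison is made at 3 and at 6 months. The section gives no covariate list and does not define baseline measurements. It also plans multiple regressions, but these look for predictors of good outcome and are not the treatment comparison.

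The design figures come from Sample size calculation and effect size. The target is a standardised difference of 0.4 and the total to be randomised is 252. Of that total the article says: "this is allowing for a 10% drop out rate, and adjusting for a 2:1 randomisation strategy".

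**The concern.** Balancing allocation on a prognostic factor removes that factor's contribution to chance differences between the arms, so the treatment estimate varies less from one randomisation to another. A model without the factor does not register this. It leaves the factor's variance in the residual and reports a standard error larger than the true spread of the estimate. Intervals are then wider than the design warrants, and the test rejects less often than its nominal 5%.

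The article names both the model and what it adjusts for, and the balancing factors are in neither. The stated purpose, to deal with possible baseline differences, also points away from them: factors balanced by design should differ little between arms, yet they belong in the model because the allocation was restricted on them. At stake is a modest amount of test power that the design has already paid for.

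**Working it through.** **Inputs from the protocol article.** Effect size 0.4 SD; 252 children, 168 and 84 by arm; 10% dropout; 2:1 allocation; three factors with 2, 2 and 3 levels, so 12 cells. The 80% power and 0.05 level are stated for the cited systematic review's calculation ("with a power of 80% at the 0.05 significance level"). I assume that they carry over to the trial's own figure and that the test is two-sided.

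**Inputs that the article does not give (assumed).** R² is the share of outcome variance remaining after the baseline score that the three factors explain; range 0 to 0.20. The correlation ρ between baseline and follow-up score is taken as 0 or 0.5.

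**1. The plan's own sample size.**
- Normal approximation: control n = (1 + 1/2) × (1.960 + 0.842)² / 0.4² = 73.6, so 74. With 148 in the intervention arm the total is 222, and 222/0.9 = 247.
- Exact t: 75 + 150 = 225, and 225/0.9 = 250. Rounded up to whole 2:1 sets this is 84 × 3 = 252, the stated figure.

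The stated size therefore takes no credit for covariates. Completers are 252 × 0.9 = 226.8 (151.2 and 75.6). With no adjustment, SE = √(1/151.2 + 1/75.6) = 0.1409, and power = Φ(0.4/0.1409 − 1.96) = 81.1% (80.7% by exact t).

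**2. Effect of the omission on the reported standard error.** The ratio of the model SE without the factors to that with them is 1/√(1 − R²):
- R² = 0: 1.000
- R² = 0.02: 1.010
- R² = 0.05: 1.026
- R² = 0.10: 1.054
- R² = 0.20: 1.118

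**3. Simulation with the baseline score in both models.** Settings: 227 children; 12 strata; permuted blocks of 3 at 2:1 within strata; ρ = 0.5; 4000 runs per setting; assumed mix of 50:50 gender, 30:70 duration and 30:50:20 age. Blocks stand in for the adaptive method, whose algorithm the article does not give. Standard errors and type I error are under no effect; power is at an effect of 0.4.

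| R² | Factors omitted: mean model SE / true spread | Type I error | Factors included: mean model SE / true spread | Type I error | Power, omitted | Power, included |
|---|---|---|---|---|---|---|
| 0 | 0.1220 / 0.1217 | 5.4% | 0.1221 / 0.1218 | 5.4% | 90.3% | 90.5% |
| 0.05 | 0.1221 / 0.1177 | 4.2% | 0.1190 / 0.1175 | 4.6% | 90.6% | 91.5% |
| 0.10 | 0.1221 / 0.1137 | 3.5% | 0.1159 / 0.1134 | 4.4% | 92.1% | 93.8% |
| 0.20 | 0.1221 / 0.1087 | 2.8% | 0.1094 / 0.1078 | 4.5% | 92.2% | 95.3% |

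The Monte Carlo standard error of a 5% rejection rate is √(0.05 × 0.95/4000) = 0.3 points.

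The model SEs confirm step 2: 0.1221/0.1190 = 1.026 and 0.1221/0.1159 = 1.053. The true spread of the estimate is almost the same in both models, because the balanced allocation has already secured it. The fault is in the reported SE and hence in the test. The power gain is 0.9, 1.8 and 3.1 points at R² of 0.05, 0.10 and 0.20.

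**4. Degrees of freedom.** Gender 1, time since diagnosis 1, age band 2: 4 in all.

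**The case against.** The strongest reply is that only a condensed article is at hand, and the exact covariate set is commonly left to a statistical analysis plan. The article never says that the baseline score is the only covariate, and it excludes nothing. The phrase baseline measurements is undefined, and the baseline questionnaire also records sociodemographic variables and patient characteristics. A reader might infer that the plan deliberately leaves the three factors out; the text does not support that. It supports only the statement that they are not named. What remains is that the article does fix a model and a reason for adjusting, and that, followed as written, neither leads an analyst to the randomisation factors.

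A reader might also infer that adjustment is triggered by observed imbalance. The sentence is unconditional, however, and describes no imbalance test or selection rule.

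Thirdly, a reader might set unadjusted power of 81.1% against 83.0% and 84.9% with the factors (R² of 0.05 and 0.10) and claim a gain of 2 to 4 points. That takes an unadjusted comparison as the starting point. The plan is an ANCOVA, so the gain has to be measured after baseline adjustment, where it is smaller and starts from above 90% if ρ is 0.5.

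Finally, the error is in the safe direction. That is correct, and it limits the weight of the point.

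**Conclusion.** The point holds in a modest and conditional form. The Statistical analysis section states the comparison model without the factors on which allocation is balanced, and the regressions for predictors do not make this good. If the factors predict outcome beyond the baseline score, the reported standard error is too large by about 2.6% at R² = 0.05 and 5.4% at R² = 0.10, and simulated type I error falls to 4.2% and 3.5%. If they do not predict outcome, nothing is lost. With a baseline correlation of 0.5, including them adds about 1 to 2 points of power at R² of 0.05 to 0.10 and about 3 at 0.20, from roughly 90 to 92%.

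It would go too far to say that the standard errors are wrong as a matter of fact, that the result would be biased, or that the trial is underpowered. The article gives no prognostic strength for the factors, omission neither biases the estimate nor inflates type I error, and about 81% power is reached with no adjustment at all. The figures rest on the assumed R² and ρ, on a two-sided 5% test, and on stratified blocks as a stand-in for the adaptive algorithm.

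**What to change.** Add one sentence to Statistical analysis: at 3 and at 6 months, the ANCOVA for the Diabetes PedsQL composite and for the other continuous outcomes (generic PedsQL, HbA1c) always includes arm, the baseline value of that outcome, and gender, age band and time since diagnosis as coded at randomisation, whatever imbalance is observed. Continuous age and duration terms may be added but are optional. The sentence need not extend to costs and service use, for which this model may not suit.

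The cost is 4 model degrees of freedom out of about 227 evaluable children. No new data are needed, since the three factors are recorded in order to randomise, and the sample size does not change.

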##### Secondary outcome measures

Secondary outcomes include: HbA1c, generic quality of life, routinely collected NHS/child-held data, costs, service use, acceptability/utility.

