#### Baseline, 3 and 6 month data collection

Children/young people (if appropriate with support of, or proxy report by parents) will complete a baseline questionnaire recording sociodemographic variables, patient characteristics, and PedsQL (generic, diabetes and parent versions). The EQ-5D will be completed by parents (as a proxy measure) as well as the child/young person.

Follow-up questionnaires, containing the same outcome measures as at baseline, and with an additional focus on process will be administered at 3 months and 6 months, (including data on health service use, episodes of diabetic ketoacidosis, and all hospital admissions for acute complications). Non-responders will receive telephone/postal reminders after two and four weeks.

Baseline and subsequent HbA1c measurements and routinely collected NHS/child-held data will be collected by the clinicians/diabetes nurse specialists/MCRN nurses, or researchers where appropriate. Blood glucose meters will be checked for the previous 250 blood glucose records if considered appropriate by the clinician and if used as part of routine clinical practice.

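### Analysis of covariance is set for outcomes of every type, and for service-use counts under 2:1 allocation its confidence intervals are the wrong width whenever the arms differ

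*Protocol article*

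**What the plan says.** The between-arm method is in the protocol article under Statistical analysis: "We shall compare outcomes between the two groups by analysis of covariance to adjust for possible differences in baseline measurements". The next sentence fixes the timing: "This will be repeated at 3 and 6 months comparing intervention and control groups". Neither sentence limits the method by type of outcome. A further analysis follows, "In addition, longitudinal analysis will consider any changes over time", and its detail is confined to one class of measure: "These analyses will examine changes in the quality of life measures". Multiple regression is added to find predictors of good outcome.

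The list under Secondary outcome measures mixes continuous and count data: "Secondary outcomes include: HbA1c, generic quality of life, routinely collected NHS/child-held data, costs, service use, acceptability/utility". The follow-up questionnaires have a process focus, "including data on health service use, episodes of diabetic ketoacidosis, and all hospital admissions for acute complications". The Methods/Design part of the abstract lists NHS resource use among the data collected at baseline, 3 and 6 months, and Economic Evaluation says "Activity will be collected for 6 months". On allocation, the sample size section says "we will employ a 2:1 randomization strategy", giving 168 and 84 children. The Uncertainty section describes the bootstrap for the cost-effectiveness analysis.

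**The concern.** Analysis of covariance suits PedsQL, EQ-5D and HbA1c. A count of health-service contacts is different: many children have none, a few have many, and the variance moves with the mean. If the intervention changes the mean, the arms no longer share a variance, but the model estimates a single pooled one. With unequal arms that estimate leans towards the larger (intervention) arm, so the standard error of the difference is too small when the intervention lowers use and too large when it raises use.

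At stake is the honesty of the interval around a named secondary outcome. It would look too precise for a reduction in service use and too vague for an increase. Separately, if each visit's comparison covers only its own 3 months, an already sparse count is divided although activity is collected over 6 months.

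**Working it through.** **Inputs.** From the article: 168 and 84 randomised, 10% dropout, effect size 0.4, 80% power, 0.05 level (two-sided assumed). Not in the article, so assumed: control mean 0.3 to 3 contacts per child over the period, and negative binomial dispersion k = 0.3 to 1, with variance = mean + mean²/k.

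**The plan's own figure.** A t-based calculation at effect size 0.4 and 2:1 allocation needs 75 + 150 = 225. Then 75/0.9 = 83.3, rounded up to 84; twice that is 168; total 252. The sample size reproduces. Children analysed: 168 × 0.9 = 151 and 84 × 0.9 = 76.

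**Why allocation matters.** Write v₁, v₂ for the arm variances.
- True variance of the difference: v₁/n₁ + v₂/n₂.
- What the pooled model estimates: [(n₁−1)v₁ + (n₂−1)v₂]/(n₁+n₂−2) × (1/n₁ + 1/n₂).
- If n₁ = n₂ = n, both equal (v₁ + v₂)/n. At 151 and 76 they differ unless v₁ = v₂.

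**Worked case, rate halved** (control mean 1, k = 0.3).
- v₂ = 1 + 1/0.3 = 4.333; v₁ = 0.5 + 0.25/0.3 = 1.333.
- Pooled: (150 × 1.333 + 75 × 4.333)/225 = 2.333; × (1/151 + 1/76 = 0.01978) = 0.0462.
- True: 1.333/151 + 4.333/76 = 0.0659.
- Standard error ratio: √(0.0462/0.0659) = 0.84. Approximate coverage: 2Φ(1.96 × 0.84) − 1 = 90%.

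**Worked case, rate doubled.**
- v₁ = 2 + 4/0.3 = 15.333. Pooled: (150 × 15.333 + 75 × 4.333)/225 = 11.667; × 0.01978 = 0.2308.
- True: 15.333/151 + 4.333/76 = 0.1586. Ratio: √(0.2308/0.1586) = 1.21. Approximate coverage: 98%.

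**Simulation** (20,000 trials per scenario, pooled-variance linear model without a baseline covariate):

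| Mean, k | Type I error | Coverage, halved | Coverage, doubled | Coverage, tripled |
|---|---|---|---|---|
| 0.3, 0.3 | 4.7% | 90.6% | 97.3% | 97.9% |
| 1, 0.3 | 4.7% | 89.3% | 97.5% | 97.7% |
| 3, 0.3 | 4.6% | 88.6% | 97.5% | 97.8% |
| 0.3, 1 | 4.6% | 91.6% | 97.4% | 98.1% |
| 1, 1 | 4.8% | 90.5% | 97.7% | 98.3% |
| 3, 1 | 4.9% | 89.7% | 97.9% | 98.5% |

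Robust Poisson intervals for the rate ratio cover about 94 to 95% in the same scenarios, with type I error of about 5 to 6%. At mean 0.3 and k = 0.3, robust Poisson detects a doubling in about 54% of trials, against 43% for the linear model.

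**Splitting the events.** Power of the linear model for a halved rate, one 3-month window against the 6-month total:
- mean 0.05 per window, Poisson: 18% against 29%;
- mean 0.1, Poisson: 28% against 49%;
- mean 0.3, k = 0.3: 44% against 56%.

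**Rare events, same data.** For a tripled rate on the 6-month Poisson total, at control rates 0.02, 0.05 and 0.10 per child, the linear model detects 20%, 58% and 89%. An exact rate test detects 17%, 55% and 87%. At 0.05, the linear model on one 3-month window detects 28%. For rare events the gain comes from not splitting, not from changing the test.

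**The case against.** The strongest objection is that this is a condensed article, that the model for secondary counts belongs in an analysis plan not shown here, and that a method introduced to adjust for baseline must be meant for scores that have a baseline. The first part stands this far: the absence of a count model is no finding in itself. But the article does state a method for outcomes without restriction, service use is on its outcome list, and the abstract gives resource use a baseline. The sentence therefore reaches service use as written, and fits it badly.

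Other parts of the objection hold and limit the point:
- Ketoacidosis and acute admissions are questionnaire items, not named secondary outcomes. A reader might infer that they will be tested by analysis of covariance; the article does not say so.
- A reader might infer that events are tested in a separate 3-to-6-month window. Recall windows are not stated, and a cumulative 6-month count is possible.
- A reader might infer that the method produces false findings of fewer events or hides harm from rare ones. With no true difference, total error stays near or below 5%; for very rare events the two tails are uneven, but the total is not inflated. On the same 6-month data an exact test is no more sensitive to a tripling.
- Costs are not left to this method alone: the bootstrap is already described for the cost-effectiveness analysis.
- Nothing in the article shows unequal variances in PedsQL, EQ-5D or HbA1c, so the method stands for those.

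**Conclusion.** The concern holds for service use. As written, the between-arm rule applies a pooled-variance model to a skewed count under 2:1 allocation. The test of no difference is sound in total error, but the interval is the wrong width when the arms differ: about 88 to 92% coverage if the rate is halved, and 97 to 98% if it is doubled or tripled. If the two visits are separate windows, power is also lost against the 6-month total.

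These sizes rest on assumed means and dispersions and on 10% dropout in each arm. They also come from a model without the baseline covariate; adjustment may reduce the variances but gives no reason for them to become equal. The point concerns a secondary outcome only. It does not support a claim that all outcomes are mishandled.

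**What to change.** Amend the statistical analysis section in two or three sentences:
- Limit analysis of covariance to the continuous scores: PedsQL, EQ-5D and HbA1c.
- Compare service-use counts once, over the full 6 months, as a rate ratio with 95% confidence interval from a negative binomial or robust Poisson model with log follow-up time as offset.
- Treat ketoacidosis episodes and acute admissions in the same way if they are compared between arms. Use an exact method only when events are too few for a model: it brings no power advantage, and an exact Poisson comparison is anti-conservative with overdispersed counts.

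No new data and no more children are needed. The cost is that these effects are reported on a ratio scale and not on the scale of the scores.

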#### Cost effectiveness analysis

We will undertake a cost-utility analysis, whereby costs are in monetary terms and outcomes are in preference-based non-monetary units such as Quality Adjusted Life Years (QALYs). The area under the curve method will be used for calculating QALYs weighting survival by quality of life weights measured using the paediatric EQ-5D instrument. We will compare our findings with the unofficial NICE ceiling of £30,000 per QALY. Discounting will not be necessary given the time period.

#### Uncertainty

The bootstrap calculation is a useful statistical approach for examining the uncertainty in cost-effectiveness analysis. It is a non-parametric simulation method used when the underlying data has a skewed distribution. The bootstrap method can be used to provide an estimate of the probability distribution of the cost-effectiveness ratio, its confidence interval, or variance in the ratio.

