##### Risks and anticipated benefits for trial participants

The research carries minimal risk and therefore it is considered appropriate to involve children and young people in evaluating the diabetes diaries and information packs [45].

We have convened an expert clinical advisory group and developed a specific clinical governance and risk management framework with diabetes clinicians to quality assure and 'sign off' children's diabetes information produced for the study as appropriate for use in the NHS (see Figure 2).

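### The only bootstrap summaries named for economic uncertainty are on the ratio scale, and they cannot be interpreted if the six-month QALY difference may lie near zero

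*Protocol article*

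**What the plan says.** Under Cost effectiveness analysis, the protocol article commits to a cost-utility analysis with QALYs from the paediatric EQ-5D: "The area under the curve method will be used for calculating QALYs weighting survival by quality of life weights". It then sets the yardstick: "We will compare our findings with the unofficial NICE ceiling of £30,000 per QALY". Under Economic Evaluation the horizon is half a year: "Activity will be collected for 6 months".

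The Uncertainty section is the only text on how economic uncertainty will be examined. Its operative sentence says that the bootstrap can be used to "provide an estimate of the probability distribution of the cost-effectiveness ratio, its confidence interval, or variance in the ratio". Each quantity it lists is a property of the ratio. The article mentions no net benefit, cost-effectiveness plane or acceptability curve.

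**The concern.** The ratio is the cost difference divided by the QALY difference. When bootstrap replicates of the QALY difference fall on both sides of zero, two things go wrong.

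- **Variance.** A ratio whose denominator has probability density at zero has no finite variance. The bootstrap still returns a number, but the few replicates closest to zero determine it.
- **Ordering.** A negative ratio can mean cheaper and better, or dearer and worse. A positive ratio can mean dearer and better, or cheaper and worse. Sorting replicates by the ratio, or drawing their distribution, discards the sign of the QALY difference and pools opposite conclusions.

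At stake is the economic conclusion. An interval, variance or distribution built this way cannot support a statement that the pack is, or is not, cost-effective at £30,000 per QALY.

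**Working it through.** **Inputs from the article.** 252 children randomised 168:84 with 10% loss (Sample size calculation and effect size); questionnaires including EQ-5D at baseline, 3 and 6 months; threshold £30,000 per QALY.

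**The plan's own figure.** The Uncertainty section gives none, so I checked the sample size, which sets the precision. For 0.4 SD, 80% power, two-sided 0.05 (sidedness assumed) and 2:1 allocation, the control arm needs 1.5 × (1.960 + 0.842)² / 0.4² = 73.6, so 74. With 148 in the intervention arm the total is 222, and 222/0.9 = 247. The stated 252 is within 3%. Completers are 168 × 0.9 ≈ 151 and 84 × 0.9 ≈ 76, about 227 in all.

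**Assumptions, because the article gives no values.** Utility SD 0.10 to 0.25; true utility gain 0, 0.02 or 0.05; cost SD £600 and cost difference £50 where costs are needed.

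**Standard error of the QALY difference.** SE = SD(QALY) × √(1/151 + 1/76) = SD(QALY) × 0.1406.

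*Model A (simple).* SD(QALY) = 0.5 × utility SD, an upper bound, and the gain holds for the whole half year. The SE runs from 0.0070 (SD 0.10) to 0.0176 (SD 0.25).

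*Model B (area under the curve).* Weights are 0.125, 0.25 and 0.125 years, the correlation between any two visits is 0.5, and the gain is present at 3 and 6 months only.
- Sum of squared weights = 0.09375. Cross terms = 0.25 − 0.09375 = 0.15625. Variance factor = 0.09375 + 0.5 × 0.15625 = 0.171875.
- At utility SD 0.2: SD(QALY) = 0.2 × √0.171875 = 0.0829, so SE = 0.0117.
- A gain of 0.02 gives 0.02 × 0.375 = 0.0075 QALYs. Φ(−0.0075/0.0117) = 26%.
- Adjusted for baseline utility: the regression slope on baseline is 0.125 + 0.5 × 0.375 = 0.3125, and the residual factor is 0.171875 − 0.3125² = 0.07422. SD = 0.0545, SE = 0.0077, and the share below zero is 16%.

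**Share of the sampling distribution of the QALY difference below zero (unadjusted, utility SD 0.10 to 0.25)**

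| True utility gain | Model A | Model B |
|---|---|---|
| 0 | 50% | 50% |
| 0.02 | 8% to 29% | 10% to 30% |
| 0.05 | under 0.1% to 8% | under 0.1% to 10% |

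**Behaviour of the ratio.** I used simulated data sets with utility SD 0.20, 151 v 76 children and up to 5000 resamples.
- *No true gain.* In one data set the bootstrap SD of the ratio was £0.39 million at 1000 resamples and £11.8 million at 5000. Percentile limits ran from about −£162,000 to +£201,000 in one data set and −£84,000 to +£104,000 in another. In two of three data sets the resamples covered all four quadrants.
- *Net monetary benefit* at £30,000, from the same no-gain resamples, gave ordered 95% intervals of −£694 to £933, −£703 to £893 and −£844 to £853.
- *Gain of 0.10 (0.5 SD).* The ratio was stable, with an SD of about £1,600 to £2,600.

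**Does the full distribution of the ratio escape the problem?** I used Model B at SD 0.2 with a normal approximation and costs independent of QALYs. The SE of the cost difference is 600 × 0.1406 = £84.
- *Gain 0.02.* Mean net benefit is 30,000 × 0.0075 − 50 = £175, with SE √((30,000 × 0.01166)² + 84²) = £360. The probability of being cost-effective is Φ(175/360) = 69%, yet 92% of ratios lie below £30,000.
- *No gain.* The probability is Φ(−50/360) = 44%, yet 91% of ratios lie below £30,000.

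The gap arises because replicates with a QALY loss also give ratios below the threshold.

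**The case against.** A reader might infer that the plan commits to reporting a confidence interval or variance of the ratio. It does not. The wording is permissive, the items are joined as alternatives, and the full distribution comes first. The neighbouring Cost effectiveness analysis section, by contrast, states its commitments with *will*. A reader might also infer that such an interval is to be compared with £30,000. The article says only that its findings will be. Both points stand and limit the criticism to what the section names.

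Nor do the documents support saying that the QALY difference *will* be near zero. They give no utility SD and no expected gain. The 0.4 SD target concerns a psychological outcome, so it neither proves nor rules out a small utility gain. If the utility gain were 0.4 SD, only 0.2% of the sampling distribution would lie below zero (Model A). Baseline adjustment, which the Statistical analysis section plans for outcome comparisons and which might extend to QALYs, also reduces the share (26% to 16% above).

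It can also be argued that a condensed article leaves presentation to a fuller economic plan, and that the resamples behind the first-listed distribution could yield a plane or acceptability curve. The absence of those outputs is indeed no fault in itself. But the article goes further than silence: it names summaries, and all share the same weakness. The 92% v 69% comparison shows that the distribution of the ratio alone does not escape it. The joint pairs of cost and QALY differences would, and the section does not name them.

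**Conclusion.** The point holds in conditional form. The Uncertainty section names only ratio-scale summaries. These are unsuitable if the six-month QALY difference is not clearly away from zero, which is plausible for an information intervention with about 227 completers. The article does not commit to any one of them.

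Under the assumed utility SDs, the wrong-sign share is 50% with no gain and about 8% to 30% for a gain of 0.02. For a gain of 0.05 it runs from under 0.1% to 8% (Model A) or 10% (Model B). For a large gain the ratio behaves well. Strictly, under a normal approximation the ratio never has a finite variance, but this matters in practice only when the probability near zero is not negligible.

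The size rests on assumed utility SDs, gains, correlation and costs. The analysis is a secondary one, and the design and primary comparison are untouched. The section is worth correcting because the summary must remain readable if the trial shows little or no QALY gain.

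**What to change.** In the Uncertainty section, state that costs and QALYs are resampled jointly by child within arm. State that uncertainty is summarised by incremental net monetary benefit at £30,000 per QALY with its interval, by the cost-effectiveness plane, and by an acceptability curve over a range of thresholds. Give the ratio as a point estimate only, and drop its variance and plain interval.

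The cost is a few sentences. The data, the bootstrap and the sample size stay as they are, and only the reported summary changes.
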